### Secondary outcome measures

#### Connor-Davidson Resilience Scale-10 items

This 10-item version of the scale [45-47] will be used to assess resilience. A higher score indicates higher resilience. The original scale shows good internal reliability and the Chinese 10-item version has shown to have good internal consistency (alpha = 0.91) and high test-retest reliability (r = .90).

#### Rosenberg self-esteem scale

It is a 10-item measure to assess global self-esteem [48] of whether participants will agree or disagree with the statements in the past 1 month on a 4-point Likert scale ranging from 1(strongly agree) to 4 (strongly disagree). Higher scores on the scale indicate higher self-esteem. One example: ‘On the whole I am satisfied with myself’. The scale has been shown to demonstrate good internal consistency and validity. The Chinese version has been shown to possess good internal consistency with alpha of 0.71.

#### Generalized self-efficacy scale

This scale contains 10 items to assess the strength of individual’s belief in their own abilities to respond to difficult situation [49,50]. Items are rated on a 4-point Likert scale, with a high total score indicating a high level of general self-efficacy. Sample item includes “I can always manage to solve difficult problems if I try hard enough”. The internal consistency (alpha = 0.86) and test-retest reliability (r = 0.75) of the original scale have been shown to be satisfactory (alpha = 0.86). The Chinese version of the scale used in the present study has demonstrated satisfactory internal consistency (alpha = 0.86).

#### Brief coping orientations to problem experienced scale (brief COPE)

Brief COPE is a 28-item questionnaire to assess behavioural and cognitive coping strategies on a 4-point Likert scale ranging from 1 (not at all) to 4 (a lot) [51]. It identifies 14 coping categories, including active coping, planning, positive reframing, acceptance, humour, religion, emotional support, instrumental support, self-distraction, denial, venting, substance use, behavioural disengagement, and self-blame. Examples of items are “I’ve been looking for something good in what is happening”, and “I’ve been blaming myself for things that happened”. The scale has been used in previous research with Chinese population [52,53]. The reliability coefficient of the instrument was 0.82 in a study with Chinese cancer patients [54].

#### General health questionnaire– 12 items (GHQ-12)

The 12-item General Health Questionnaire is used to assess the severity of non-psychotic psychiatric disturbance during the last month [55]. Sample items include ‘Been feeling unhappy and depressed’ and respondents indicate on a 4-point scale (1 = less so than usual; 4 = much more than usual) when a higher global distress score implies a higher level of psychological disturbance. The Chinese version yields satisfactory internal reliability, with alpha values ranging from 0.87 to 0.93.

#### Perceived stress scale – 4 items (PSS-4)

PSS-4 [56] contains 4-item to measure overall stress perceived by participants in the past one month. They indicate whether their lives are unpredictable, uncontrollable or overloaded on a 5-point Likert scale ranging from 0(never) to 4 (very often). A sample item includes “in the last month, how often have you felt that you felt that things were going your way”. The psychometric properties of Chinese version have been shown to be satisfactory with alpha value 0.67 and concurrent validity.

#### Risk and sexual risk behaviours

Other information on risk behaviours collected includes sexual acts, number of partners, other risk behaviours such as smoking, drug /alcohol use and dependence, health seeking behaviour, and HIV/ STI testing will also be elicited in the questionnaire.

#### Socio-Demographic information

Information to be collected includes participants’ age, years of formal education, marital status, living arrangements, monthly income and length of time working in sex industry.

### Process evaluation

The process evaluation will examine the fidelity of intervention on five different domains proposed by the National Institutes of Health Behavior Change Consortium (BCC) [57], namely design of study, training provider, treatment delivery, receipt of treatment, and enactment of treatment (see Table 2). If the programme is found to be effective, a cost-effectiveness evaluation will then be conducted.

**Table 2 T2:** Process evaluation of PREP

**Areas**	**Goals**	**Strategies**
*Design of study*	1. To ensure intervention is developed based on relevant theory.	Literature review was conducted; intervention is based on resilience framework.
	2. To ensure “dose” across is adequately described.	Participants in intervention arm will received 6 one-hour sessions and each session one-to-three week apart; field note of each session and service received by the participants will be recorded.
*Training of provider*	3. To ensure group facilitator acquires the skills and sustains over time.	Use standardized training manuals and materials for training; role playing the sessions; external quality assurance through bi-weekly meeting with investigative team throughout the study.
*Delivery of treatment*	4. To ensure intervention delivered adheres to treatment protocol and minimize differences within intervention.	Use of an intervention manual; facilitator will take field notes of the session; Helpers will rate the adherence with a checklist; have member of investigative team to observe selected sessions; record any protocol deviations.
	5. To minimise contamination between intervention and control conditions.	Advise participants not to disclose the condition they are in; conduct interviews with selected participants in control group to ensure they do not receive treatment; train the staff of NGOs the rationale of the two conditions.
*Receipt of treatment*	6. To ensure participants understand the information provided in the sessions and they are able to perform the skills learnt.	Use of active questioning to assess their understanding; record their attendance; rate their involvement in each session by group facilitator, participants and/or session helper; Use discussion role-play to ensure participants’ understand the contents.
*Enactment of treatment*	7. To ensure participants utilise the skills introduced in the intervention sessions.	Use of homework to encourage they use their skills between sessions; discuss how they have used the skills in daily life in sessions.

An intervention manual will be used and the adherence to the manual will be constantly monitored by facilitator and investigative team throughout the study. In addition, the group facilitator will also write field notes at all stages of the research process. At the same time, the involvement of the participants on their understanding and use of the skills learnt in the sessions will be rated by the group facilitator. At post-intervention, the participants will be invited to provide feedback on their satisfaction of the programme with a Likert scale and some open-ended questions. A bi-monthly meeting will be held by the investigative team and representatives of the NGOs and sex workers for progress monitoring and program feedback. Any adverse effects of the study will be reported to the NGOs where details can be recorded and reported and discussed at the meetings. These assessments will provide information on the intervention delivery and receipt process, and allow ecological validity to the data.

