### Participants

FSWs who fulfil the inclusion criteria will be invited and have the study explained to them by the trained outreach staff of the NGOs. Inclusion criteria for the proposed study are: (i) 18 years or older; (ii) acknowledged to have been living and working as a FSW in Hong Kong within the preceding 6 months; and (iii) able to give an informed consent. All potential participants will be screened over the telephone by one of the researchers who is a clinical psychologist to confirm their fulfilment of inclusion criteria and exclude them if they are (i) unable to speak Cantonese/ Putonghua; and (ii) diagnosed with and currently on medical or psychological treatment for a serious psychological health problems such as psychosis, current substance abuse, bipolar disorder, severe affective disorders or have suicidal ideation.

Eligible participants will be provided with further details of the study and those who provide verbal consent will complete the self-reported baseline questionnaire face-to-face. Participants will be randomly allocated on a 1:1 ratio into one of the two groups according to a block randomisation list which was computer-generated. Participants are informed that they would have an equal chance of allocating into any of the two groups and the allocation outcome is unknown to participants until baseline assessment session. The women recruited will be advised not to disclose the content and activities of the intervention to others to avoid contamination. An independent researcher will conduct the baseline, post-intervention, and follow-up assessments and enter the data obtained from the questionnaires.

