### Intervention procedure

Participants in the intervention group will receive 6 one-hour group sessions at one-to-three week intervals. There will be 3 to 6 participants in each group. These sessions target at the three major psychological resilient factors of self-esteem, self-efficacy (e.g. praise and self-rewards will be used) and coping flexibility based on resilience framework. The programme will be conducted in a group setting so that role-plays and group modelling and interactions will be used. Such an approach, informed by Social Cognitive Theory [34], espouses that individuals can learn from the actions of another person and from the regular reinforcement a person receives. Activities in these sessions will incorporate examples of their experience in daily life and at work aimed at promoting their awareness and expression of their emotions and thoughts, management of their emotions. Since the current intervention aims to promote psychological well-being, it also draws on the approach used by previous resilience interventions, including recognising and sharing positive thoughts and emotions, identifying personal strengths and ability, introducing a variety of coping strategies, and planning using their skills and strengths to achieve goals in the future. The outline of each session is listed in Table 1.

**Table 1 T1:** Programme Outline of PREP

**Session**	**Contents**
1. Starting out	Goal-setting, encouraging awareness and expression of emotions in reaction to events
2. Empowering interpretation	Emotion management, identifying negative thoughts and generating helpful thoughts
3. Effective problem-solving	Exploring effective coping strategies, practicing problem-solving with case scenarios
4. Who am I?	Recognising their roles, giving each other affirmation
5. The unique self	Identifying successful experiences and their strengths, expressing gratitude to others
6. Preparing for the future	Exploring obstacles and using their resources to deal future challenges

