### Usual care

Participants who are assigned to the control group will receive the standard service provision currently provided by the NGOs. Currently, the two local NGOs offer regular outreach visits and voluntary HIV/ STIs screening. Some FSWs also choose to join activities organised by the NGOs (e.g. yoga, English class or gathering). For this study, the usual service provision includes outreach visits made by the NGOs (usually the same venue will be visited once to twice a month), attending HIV/STI screening, and social activities according to their own needs and schedule. The nature of these contacts initiated by the outreach workers or sex worker themselves will be recorded. They will be advised not to join any additional psychological programmes during the study period or they have to leave the trial.

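### Reports of adverse effects that depend on attribution to the study and go to the NGOs would not be comparable between arms, and would probably show more harms under PREP

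*Protocol article*

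**What the plan says.** The article deals with harms in one sentence, in the Process evaluation section: "Any adverse effects of the study will be reported to the NGOs where details can be recorded and reported and discussed at the meetings". The meetings in question are the bi-monthly ones between the investigators, the NGOs and sex worker representatives.

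Contact differs by arm. Under Intervention procedure, "Participants in the intervention group will receive 6 one-hour group sessions at one-to-three week intervals". The facilitator writes field notes, and Table 2 adds involvement ratings, helpers with an adherence checklist and observation of selected sessions. Under Usual care, controls receive outreach, for which "usually the same venue will be visited once to twice a month", together with "attending HIV/STI screening, and social activities according to their own needs and schedule". The nature of these contacts is recorded.

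Both arms share the assessments. Under Participants, "An independent researcher will conduct the baseline, post-intervention, and follow-up assessments". Study design has outcome measures collected from all participants at baseline, at the end of the intervention (6 to 12 weeks after baseline for controls) and 3 months later. GHQ-12 is a secondary outcome with a one-month recall period, and Data analyses plans to compare its change between groups by analysis of variance under intention to treat.

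**The concern.** Two features of the stated route act differently by arm.

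The first is attribution. The rule concerns effects of the study. Apart from assessments and instructions, the study gives control women nothing beyond existing NGO services. An episode of self-harm, an assault or a worsening of distress in a control woman would hardly be called an effect of the study. The same event in a woman who has just taken part in emotion-focused group work plausibly would be.

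The second is opportunity. An event has to be noticed or mentioned before it can be reported, and PREP women are seen more often, by people who keep notes.

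Both features push towards more recorded harms under PREP, even if the true rates are equal. The Background names self-harm, anxiety, depression and violence as risks in this population, so background events are to be expected in both arms. A safe programme could look harmful, and a real excess could be put down to closer observation. The counts could not settle which is true.

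**Working it through.** The article gives no harms figure and no contact ratio, so there is no stated figure to reproduce. The ratios below are derived.

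**Inputs**
- PREP sessions: 6 (Intervention procedure).
- Outreach: 1 or 2 visits per month to the same venue (Usual care).
- Intervention period: 6 to 12 weeks (the control timing in Study design).
- Further follow-up: 3 months, taken as 13 weeks (Study design).
- Weeks per month: 52/12 = 4.33.

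**Assumptions**
- PREP women keep the same outreach visits. The article suggests this, since outreach staff follow up the women recruited, but does not state it outright.
- One venue visit is one contact per woman.
- Optional screening and social activities are left out because no number is given.

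**Formulas:** control contacts C = weeks / 4.33 × visits per month; ratio = (6 + C) / C.

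| Period | Visits per month | Control C | PREP 6 + C | Ratio |
|---|---|---|---|---|
| 6 weeks | 1 | 1.38 | 7.38 | 5.33 |
| 6 weeks | 2 | 2.77 | 8.77 | 3.17 |
| 12 weeks | 1 | 2.77 | 8.77 | 3.17 |
| 12 weeks | 2 | 5.54 | 11.54 | 2.08 |
| 6 + 13 weeks | 1 | 4.38 | 10.38 | 2.37 |
| 6 + 13 weeks | 2 | 8.77 | 14.77 | 1.68 |
| 12 + 13 weeks | 1 | 5.77 | 11.77 | 2.04 |
| 12 + 13 weeks | 2 | 11.54 | 17.54 | 1.52 |

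The ratio is thus 2.1 to 5.3 during the intervention and 1.5 to 2.4 over the whole study.

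**Sensitivity**
- Five intervals of one to three weeks give a course of 5 to 15 weeks. The intervention-period ratio is then 1.9 to 6.2.
- Adding the post-intervention assessment to both arms, over 6 to 12 weeks, (7 + C) / (1 + C) = 1.9 to 3.5.
- Adding all three assessments to both arms, over the whole study, (9 + C) / (3 + C) = 1.4 to 1.8.
- If PREP women had no outreach at all, 6 / C = 1.1 to 4.3 over 6 to 12 weeks. It falls below 1 only for a 15-week course at two visits a month: 6 / 6.92 = 0.87.

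The direction therefore holds in every scenario but that last one. The attribution problem needs no ratio.

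**What GHQ-12 covers.** Its recall period is one month. Of the 3 months between the post-intervention and follow-up assessments, about 3 − 1 = 2 months are not asked about. Of the 6 to 12 weeks before the post-intervention assessment (1.38 to 2.77 months), about 0.4 to 1.8 months are not. It is planned as change in scores, and a group mean can improve while a minority gets worse. It measures the severity of non-psychotic disturbance and does not record events such as self-harm or violence.

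**The case against.** **The article is a condensed account.** Definitions, forms and elicitation may sit in the full protocol, and their absence here is not a defect. This is right, and the point does not rest on it. It rests on the rule that is stated, which fixes both what counts (effects of the study) and where it goes (the NGOs). If the full protocol collects harms equally in both arms, this sentence misdescribes it and should be aligned.

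**No comparison of harms by arm is planned.** The sentence serves process monitoring, and Data analyses contains no harms count. This also stands. The defect takes effect only when the reports are set side by side by arm, so it is one of design and not an error in a stated analysis.

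**Symmetric measures exist.** GHQ-12, the perceived stress scale, drug and alcohol use and health-seeking behaviour are collected in both arms. A reader might infer from the harms sentence that the trial cannot detect worsening at all. The documents do not support that: average distress is compared between arms on the same schedule. What GHQ-12 leaves open is events, the months outside its recall period and worsening in a minority.

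**The sessions are not NGO contacts.** They are led by a psychologist, whereas the reporting route runs to the NGOs. This weakens the contact ratio somewhat. However, the sessions are held in the NGOs' service centres, and the investigators meet the NGOs regularly, so an event noticed in a session has a path into the route.

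**Two further inferences do not hold.** The article does not say that reports must be volunteered; it simply describes no active enquiry. Nor does the advice on confidentiality show that women are discouraged from reporting harm. They are "advised not to disclose the content and activities of the intervention to others to avoid contamination", which concerns session content, and NGO staff are trained in the rationale of both conditions.

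**Conclusion.** The concern holds for counts of adverse effects reported through the stated route. Those counts would not be comparable between arms and would probably be biased towards more recorded harms under PREP. The attribution requirement is enough to establish this; unequal contact adds to it.

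The size of the contact imbalance, about 2 to 5 times in the intervention period and about 1.5 to 2.4 times over the whole study, is derived and rests on the assumptions listed above. The larger range should not be read as applying to the whole trial. The size of the resulting bias in counts cannot be worked out, because the article gives neither event rates nor the chance that an event is disclosed.

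The efficacy analysis is unaffected, and the comparison of average distress by GHQ-12 remains available.

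**What to change.** Amend the harms sentence under Process evaluation as follows.

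1. At the post-intervention and 3-month assessments, the independent researcher asks every woman in both arms the same short, fixed set of harms questions, covering the period since the last assessment. New or worse distress, self-harm and violence are examples; the investigators should settle the list.
2. Answers are recorded whatever the presumed cause. Any judgement about relation to the study is noted separately and does not decide whether an event is counted.
3. Events are tabulated by randomised arm, alongside the share of women whose GHQ-12 score worsened from baseline, which uses data already planned.
4. Reports to the NGOs continue as a monitoring route and appear as a separate listing that is not used for comparison between arms.

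The cost is a few questionnaire items at two visits that already take place and one extra table, with no new visits or staff. The downside is a few more minutes per visit and more background events recorded in both arms, which should be expected and explained when the results are reported.

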### Data analyses

First of all, the baseline demographics of the intervention and control groups will be compared with independent sample *t*-tests for continuous variables and *chi*-square for categorical variables to assess the compatibility of the two-trial arms at baseline to ensure both groups were similar to start with. The change of scores on sexual health risks and psychological outcome measures (self-esteem, self-efficacy, coping, resilience and GHQ) over time between two groups will be analysed using analysis of variance with intention-to-treat analysis. Bivariate correlation analyses will be performed to examine the relationship between psychological variables and behavioural outcomes. Linear regressions will also be used to examine the associations and the effects of resilience, self-esteem, self-efficacy, coping on psychological health outcomes and HIV preventive behaviours. The statistical analyses will use SPSS 20.0 and *p*-values of 0.05 or less will be considered statistically significant.

The second objective of the current study is to explore the mechanism of how individual resilience factors influence the psychological outcomes and HIV preventive behaviours in FSWs (as proposed in Figure 1). Structural equation modelling (SEM) identifies connection strengths that best predict the observed structure of the data with respect to the specified model. Thus, SEM will be performed to evaluate the model fit of the proposed model that links psychological resources with harm-reduction behaviours as measured by condom use.

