### Sample size

Sample size estimation is based on the “always” use condom rate during commercial transactions in the last month at 49.3% from the latest local study published on the topic [16] and an assumption of effect size of 25% on condom use rate between the intervention and control groups from a previous study [43]. In order to detect such a difference with a power of 80% and a two-tailed significance of 0.05, the sample size required is 66 in each group.

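### Baseline significance tests cannot ensure that the arms are similar, and the planned ANOVA of change uses baseline without adjusting for it

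*Protocol article*

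**What the plan says.** The Data analyses section opens with a comparison of baseline demographics, which "will be compared with independent sample" t-tests if continuous and chi-square tests if categorical. The stated purpose is "to assess the compatibility of the two-trial arms at baseline to ensure both groups were similar to start with". The same paragraph sets the general threshold: p-values "of 0.05 or less will be considered statistically significant".

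The section headed Socio-Demographic information lists the variables concerned: "Information to be collected includes participants’ age, years of formal education, marital status, living arrangements, monthly income and length of time working in sex industry". That is six variables. Allocation, described under Participants, is 1:1 from a computer-generated block list. The planned size is given under Sample size: "the sample size required is 66 in each group".

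For the outcomes, Data analyses plans an analysis of variance of change over time between the two groups, by intention to treat. This covers sexual health risks as well as the psychological scales. The section does not say what a significant or non-significant baseline test would lead to, and it names no baseline covariate for the outcome comparison.

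**The concern.** The baseline tests are given a task that they cannot perform. Under a sound random allocation the null hypothesis of each test is true by design. A small p-value is then a chance finding, and a large one does not show that the two samples are alike. What matters for the treatment estimate is how far the arms happen to differ on variables that predict the outcome, whatever the p-value.

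The outcome analysis does not deal with that either. Taking change from baseline is not the same as adjusting for baseline. It subtracts the whole baseline difference, although only a fraction of it (the regression slope of follow-up on baseline) is expected to persist to follow-up. If the intervention arm happens to start higher on condom use, the change analysis understates its effect; if it starts lower, the effect is overstated.

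At stake are a false assurance about comparability in the trial report, and a primary estimate that is conditionally biased and less precise than the same data allow.

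**Working it through.** **Inputs from the protocol article.** 66 per arm; two-sided 0.05 and 80% power; a 49.3% always-use rate; a 25% effect, read as percentage points (49.3% against 74.3%); six demographic variables.

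**Assumed, because the article gives no value.** The baseline-to-follow-up correlation ρ, taken as 0.3 to 0.7; equal outcome variance at both times; the same slope in both arms. For always-use the outcome is treated as 0/1 on the linear scale.

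**1. The plan's own figure.** The two-proportion formula with mean proportion 0.618 gives

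[1.960·√(2·0.618·0.382) + 0.842·√(0.493·0.507 + 0.743·0.257)]² / 0.25² = 58.1.

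The continuity correction gives (58.1/4)·[1 + √(1 + 4/(58.1·0.25))]² = 65.9, so 66 per arm. The stated size reproduces, which supports the percentage-point reading.

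**2. What the baseline tests can see.** An observed standardised difference is significant only above t(0.975; 130)·√(2/66) = 1.978 × 0.174 = 0.344 SD. Anything smaller passes every time.

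**3. How often the tests flag a sound randomisation.** With six independent tests, 1 − 0.95⁶ = 26.5%. Correlated variables, such as age and time in sex work, would lower this.

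**4. How often a sizeable gap in baseline always-use arises by chance.** The standard error of the difference is √(2·0.493·0.507/66) = 8.70 points. For 15 points, z = 15/8.70 = 1.72, so the two-sided probability is 8.5%. Counting exactly, a gap of 10 or more women (15.2 points) has probability 9.8%. Hence roughly 8 to 10%.

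**5. What the change analysis does with such a gap.** If the arms differ by δ at baseline, the expected follow-up difference without any effect is ρδ. The change analysis subtracts δ, which leaves an error of −(1−ρ)δ. For δ = 15 points:

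| ρ (assumed) | Size of error, (1−ρ)·15 |
|---|---|
| 0.3 | 10.5 points |
| 0.5 | 7.5 points |
| 0.7 | 4.5 points |

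At ρ = 0.5 this is 7.5/25 = 30% of the target effect, in a trial that has drawn such a gap. Over all randomisations δ averages zero, and so does the error.

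**6. Precision.** Relative to a comparison of follow-up values alone, the variance is 2(1−ρ) for change and 1−ρ² for baseline adjustment. Their ratio, adjusted to change, is (1+ρ)/2.

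| ρ (assumed) | Change | Adjusted | Ratio |
|---|---|---|---|
| 0.3 | 1.40 | 0.91 | 0.65 |
| 0.5 | 1.00 | 0.75 | 0.75 |
| 0.7 | 0.60 | 0.51 | 0.85 |

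The adjusted analysis is never the less precise of the two. Below ρ = 0.5 the change analysis is also less precise than the plain follow-up comparison of proportions on which the sample size rests.

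**The case against.** The strongest defence is that this is one loosely worded sentence. Testing baseline demographics is common, nothing in the article is said to depend on the result, and deleting the tests alone would alter no estimate. All of that stands. So does the reply that the change-score error has nothing to do with the demographic tests: it depends on a chance imbalance in the outcome itself, vanishes on average, and leaves type I error intact.

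Three stronger readings are tempting, and the article does not support them.

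- A reader might infer that the tests would miss a relevant imbalance most of the time, by computing their power against, say, a 0.3 SD difference. That is power against a true population difference, which sound randomisation rules out, and the article defines no relevant size. The observed difference is what counts, and for it the 0.34 SD cut-off is the useful figure.
- A reader might infer that imbalance will go uncorrected. The article does not say so. Each outcome's baseline already enters through the change analysis, and covariates may be listed in an analysis plan that is not shown.
- A reader might want length of time in sex work added as a covariate. It is collected, but nothing in the article shows that it predicts condom use.

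What the defence does not answer is that the article states both things itself: an inference from the tests that cannot be valid, and a change analysis that is less efficient than adjustment. Neither is a detail merely left for later.

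**Conclusion.** The point holds, at minor to moderate weight. The baseline tests cannot ensure similarity: they pass any continuous difference below about 0.34 SD, and they flag about 26% of sound randomisations if the six tests are independent. That part affects what the report may claim, not the treatment estimate.

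The part that bears on the estimate is the ANOVA of change. In the roughly 8 to 10% of trials with a chance gap of 15 points or more in baseline always-use, a gap of exactly 15 points moves the estimate by 4.5 to 10.5 points, and larger gaps move it proportionally more. In every trial the variance is higher than under baseline adjustment, with a ratio of 0.65 to 0.85 in favour of adjustment. These ranges rest on an assumed ρ of 0.3 to 0.7, equal variances and a linear scale. The direction does not depend on the exact ρ as long as it is below 1. The validity of the randomised comparison is not in question.

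**What to change.** - Remove the baseline t-tests and chi-square tests, together with the claim that they ensure similarity.
- Describe baseline by arm with summary statistics, and include baseline condom use beside the demographics.
- Replace the ANOVA of change with a between-arm comparison at follow-up adjusted for the baseline value of the outcome being analysed. For the psychological scales this is a linear model with the baseline score as covariate. For always-use it is a binary-outcome model with baseline always-use as covariate, preferably reported also as a difference in percentage points to match the sample size assumption.
- Fix this adjustment in advance and apply it whatever imbalance is observed.

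Outcome measures are already collected at baseline, so no new data are needed and the sample size does not change. The cost is a revision of the analysis text and about one model degree of freedom per outcome.
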